## Abstract

**Background:**

Metabolic syndrome is a set of disorders that increases the risk of developing cardiovascular disease. The primary target of treatment of patients with metabolic syndrome is therapeutic lifestyle change. Numerous preclinical study have reported positive effects of chungkookjang in *in vivo* models of diabetes and obesity, but there is a paucity of controlled clinical trials on variables of metabolic syndrome in obese subjects. Thus, the objective of this trial is to examine the effect of chungkookjang compared to placebo on variables of metabolic syndrome in overweight/obese subjects.

**Methods:**

This double-blind randomized controlled crossover trial will be conducted on 120 overweight/obese subjects; aged 19–29 years. Subjects will be recruited from the Chonbuk National University, Jeonju, South Korea. Enrolled subjects will be randomly assigned to two groups of equal number; one group received 35 g of chungkookjang (n = 60) and the other group received placebo (n = 60) on a regular daily basis for 12 weeks. After a 12-week washout period, the groups will be crossed over. In addition to anthropometric measures and blood pressure, glucose parameter, lipid profile, adipocytokine, and carnitine assay will be determined at baseline and 12 week. Also, safety will be assessing by measuring total bilirubin, alkaline phosphatase, alanine transaminase, aspartate aminotransferase, total protein, albumin, blood urea nitrogen, creatinine, and creatine kinase at baseline and 12 weeks. 24-hour dietary recalls were collected at the baseline and at the end of the trial.

**Discussion:**

This trial will evaluate the effects of chungkookjang on variables of metabolic syndrome in overweight/obese subjects. The results of this study may contribute to the reduction of risk factor for metabolic syndrome caused by obesity.

**Trial registration:**

Clinical trials NCT01811511.

## Background

The prevalence of obesity has increased worldwide over the past decades [1,2], although more recent data suggest a slowing of this trend. The rising rates of obesity in children and adults have been accompanied by an increase in the co-occurrence of obesity-associated metabolic abnormalities known as the metabolic syndrome (Met-S). The prevalence of Met-S is increasing; it currently affects 22.1% of men and 27.8% of women in Korea [3,4]. The clustering of major components of the syndrome, including obesity, dyslipidemia, hypertension, and insulin resistance, has been demonstrated in youth [5,6], and clustering of these risk factors has also been shown to track into early adulthood. These obese youth are a high-risk population to target for screening, prevention, and intervention for Met-S [5,6].

Conclusions in nutritional intervention studies are frequently drawn from epidemiological studies, but there are affected by many possible confounding factors. Unlike laboratory animals, human beings cannot be fed over a long time; thus most nutritional intervention studies are short to medium term and focus on surrogate parameters. On the other hand, although the preferred treatment for Met-S is lifestyle modification including exercise and nutrition therapy [7,8], the challenge is the multitude of risk factors and the high prevalence of obesity. But there are difficult to approach in typically clinic visits. Furthermore, in the large scale trials, subjects often struggle with adopting lifestyle changes to derive siginificant results, but it is difficult to control the subjects by physician or investigators.

Soybeans contain various nutritious and functional components such as isoflavonoids besides soy protein which are helpful in protecting against metabolic diseases such as obesity and type 2 diabetes [9]. Fermenting soybean such as chungkookjang (CKJ) may be enhance the functionality of soybeans to protect against metabolic disease. Korean traditional CKJ is a good fermented soybean product for use as a functional food. However, traditional CKJ did not recognized as a functional food in Korea. Currently, the non-clinical data on effects of CKJ have been reported from in vivo and in vitro studies [10-18] but there is paucity the controlled clinical trials on variables of Met-S. Our previous study have revealed that traditionally made CKJ from Sunchang district of Jeolla province, Korea showed potential anti-atherosclerotic effects in overweight/obese subjects [19]. It has also been reported that traditional CKJ (made from Sunchang district of Jeolla province, Korea) improves insulinotropic action and hepatic insulin sensitivity in diabetic rats [16,17].

However, CKJ intake in Korean youth is gradually decreased due to distinctive flavor of CKJ. Therefore, the present study will be conducted by the easy-to-eat freeze-dried CKJ pills. The CKJ shows distinctive flavor characteristics. For this reason, we used cinnamon as flavoring agent to make it palatable. The purpose of this study is to evaluate the effect of CKJ compared to placebo on variables of Met-S in overweight/obese subjects.

## Methods and design

### Objective

The objectives of this RCT are to study whether the CKJ can improve the Met-S in overweight/obese subjects.

#### Primary objective

To evaluate the efficacy of the CKJ on anthropometric parameter in overweight/obese subjects after 12 weeks of consumption.

#### Secondary objectives

To evaluate the following factors in overweight or obese subjects after 12 weeks of consumption on:

A) blood pressure

B) glucose parameter

C) lipid profile

D) adipocytokine

E) carnitine assay

### Design and setting

This is a 12 weeks, randomized, double-blinded, placebo-controlled crossover study. From February 2013 to December 2013, Obesity Research Center of Chonbuk National University and Chonbuk National University Hospital Clinical Trial Center in Korea will participate in this study. Recruitment will therefore be expected to be completed within the study period. To recruit the participants, we will advertise in the bulletin board and on the internet homepage of Chonbuk National University. Eligible participants will be randomly allocated into 2 group (the CKJ or placebo group) with 1:1 allocation ratio and receive treatment for 12 weeks. After a 12-week washout period, the groups will be crossed over. The evaluation of participants and the analysis of the results will be performed by professional blinded to the group allocation. Written consent will be obtained from each participant before the start of this study. Our study plan is summarized in Figure 1.

**Figure 1 F1:**
[figure not shown]
**Flow diagram for study.** Summary of the study flow.

### Inclusion criteria

Subjects will be included if they meet the following criteria: (1) men and women between 19 and 29 years of age; (2) overweight/obese (body mass index of 23 kg/m2 or a waist circumference of 90 cm for men, 80 cm for women); (3) ability to give informed consent.

### Exclusion criteria

The exclusion criteria for the study were: (1) severe heart disease (heart failure, angina, myocardial infarction, valvular heart disease, arrhythmias); (2) severe cerebrovascular disease (stroke, hemorrhage); (3) acute or chronic inflammatory disease; (4) malignant tumor (leukemia, lymphoma); (5) diagnosis of type 1 and type 2 diabetes or fasting glucose ≥ 126 mg/Dl; (6) Systolic pressure ≥ 160 mmHg, diastolic pressure ≥ 100 mmHg; (7) hereditary hyperlipidemia; (8) allergic or hypersensitive response to any of the ingredients in the test products; (9) a history of disease that could interfere with the test products or impede their absorption such as gastrointestinal disease or gastrointestinal surgery; (10) under antipsychotic drugs therapy within past 2 months; (11) participation in any other clinical trials within past 2 months; (12) abnormal hepatic liver function or renal disease (acute/chronic renal failure or nephrotic syndrome); (13) laboratory test, medical or psychological conditions that might interfere with successful participation in the study based on the judgment of the investigators.

### Randomization and allocation concealment

After enrollment, subjects will be randomly assigned to one of the two groups, either the CKJ group or placebo group. The allocation ratio will be 1:1 in blocks of 2. Randomization will be performed at a site remote from trial location. Random numbers will be generated by a computerized random-number generator through the block-randomization method of a software program (Excel, Microsoft Office 2007) for sequence generation. At the time of randomization subjects will draw an envelope. Each envelope contains a number that is concealed to the treatment allocation. Randomization sequence and allocation will be concealed to all study subjects, research staff, investigators and pharmacists until completion of the study. The allocation list will be protected by password access files and held by a non-investigator independent. In the event of an emergency medical situation the individual’s randomization code and group allocation can be identify.

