#### Sample size

Sample size calculation is performed; primary outcome measure will be the percentage body fat, whereby 1.1% is assumed a clinically relevant difference between the two groups, with a standard deviation of 2.78%, alpha set on 5% and power on 80%. This resulted in a required number of 50 subjects in each group. Assuming a dropout rate of 20%, a total of 120 subjects will be enrolled in this trial.

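### Fixed blocks of 2 mean that once one subject's allocation is known, by code break or inference, the paired subject's sequence is known with certainty

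*Protocol article*

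**What the plan says.** All references are to the protocol article.

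- **Randomization and allocation concealment** fixes the scheme: "The allocation ratio will be 1:1 in blocks of 2". No second block size, variation or stratification is mentioned. The list comes from a "computerized random-number generator through the block-randomization method of a software program (Excel, Microsoft Office 2007) for sequence generation".
- The same section describes delivery: "At the time of randomization subjects will draw an envelope". It does not say whether envelopes are taken in list order.
- It states the aim of concealment: "Randomization sequence and allocation will be concealed to all study subjects, research staff, investigators and pharmacists until completion of the study". The list is generated away from the trial site, password-protected, and held by someone who is not an investigator.
- It also allows for emergencies, in which an individual's "randomization code and group allocation can be identify".
- The **Abstract** and **Sample size** sections give the numbers: "Enrolled subjects will be randomly assigned to two groups of equal number", and "a total of 120 subjects will be enrolled in this trial".
- **Design and setting** describes a two-period crossover with a 12-week washout, so the allocation fixes what a subject receives in both periods.
- **Background** says of the product: "The CKJ shows distinctive flavor characteristics". It adds that cinnamon was used to make the product palatable. **Intervention** says that the placebo matches the product in taste, appearance and energy.

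**The concern.** A block of 2 at 1:1 has only two possible orders, AB and BA. The two members are always opposite, so knowledge of one is knowledge of the other. No larger block has this property from a single known allocation.

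The article itself provides one way for an allocation to become known before the end of the study, the emergency code break. Inference from taste or side effects is another possible way. In either case, anyone who knows the block size and can match list numbers learns a second subject's sequence, contrary to the section's own aim of concealment until completion.

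That knowledge could matter at several points. Eligibility is rechecked at Visit 2 (Table 1), and exclusion criterion 13 rests on investigator judgement. Diet and exercise counselling runs through the visits. The primary outcomes include waist and hip circumference, which depend partly on the person measuring.

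**Working it through.** **Inputs.** Block size b = 2 and ratio 1:1 (Randomization and allocation concealment); N = 120 (Sample size); 60 per group (Abstract).

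**The plan's own figure.** 120 / 2 = 60 blocks. Each holds one subject who starts on the product and one who starts on placebo, which gives 60 + 60 = 120. The stated group sizes are reproduced.

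**Effect of one known allocation.** In a block of size b, if one member's allocation is known, the probability that a given other member is in the opposite group is (b/2)/(b − 1):

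- b = 2: 1/1 = 1.00
- b = 4: 2/3 = 0.67
- b = 6: 3/5 = 0.60

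This is the cleanest comparison, because it needs only one leaked allocation and no assumption about taste.

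**Share of allocations determined by earlier ones in the block.** An allocation is determined when one group's places in the block are already used up.

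- b = 2: the second of each pair, so 1/2, or 60 of 120.
- b = 4: of the 6 possible orders, 2 (AABB, BBAA) have the last two places determined and 4 have only the last. The expected number is (2×2 + 4×1)/6 = 4/3 per block, so (4/3)/4 = 1/3, or 40 of 120.
- b = 6: enumeration of all orders gives 1/4, or 30 of 120.

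These shares assume that all earlier allocations in the block are known. In blocks of 4 that means at least two others; in blocks of 2 a single one is enough.

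**Best-guess accuracy when earlier allocations are known.** For b = 2 the first is a coin toss and the second is certain: (0.5 + 1)/2 = 75%, or 90 of 120. Enumeration gives 70.8% for b = 4 and 68.3% for b = 6. Simple randomisation gives 50%.

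**Partial knowledge.** If the first member is guessed correctly with probability p, the second is predicted correctly with the same p. At p = 0.5, where the blind holds, the block rule adds nothing.

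**Balance.** Within a block the two groups can differ by at most b/2: 1 subject for b = 2, 2 for b = 4, 3 for b = 6. Fixed blocks of 4 or 6 both divide 120 exactly (120/4 = 30; 120/6 = 20).

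**The case against.** The strongest reply is that the block rule discloses nothing by itself. The sequence is generated remotely and held independently, and envelopes contain only a number. The article does not show that site staff knew the block size during recruitment. A reader might infer that every second allocation is simply predictable; the documents do not support that. The 60 of 120 applies only once the first member's allocation is known. **This stands.**

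A reader might also infer that the blind fails because of the flavour. That is not documented. The placebo is stated to match in taste and appearance, and the cinnamon is described as serving palatability, not masking. A subject who recognises the product is unblinded under any block size. Subjects can compare the two products only from week 24 (12 weeks of treatment + 12 of washout), by which time the block-mate would normally have been allocated. **This stands too:** failed masking is a risk, not a fact.

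A third tempting reading is that drawing envelopes undoes the blocks. It rests on one loosely used word. If envelopes were drawn out of order, the next enrolee would be harder to predict, but 60/60 would still result once all 120 were used. If the numbers are list numbers, the pairs would remain exposed to a code break.

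The crossover softens the consequences. Everyone receives both treatments, so foreknowledge concerns order only. Blinded evaluation is stated, and each break exposes at most one further subject. Blocks of 2 also have a real merit: they keep the groups within 1 of each other throughout recruitment.

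None of this removes the core. The block size is a stated choice, not a detail left to another document, and nothing in the article offsets the complementary pairing.

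**Conclusion.** The point holds in conditional form. Given one known allocation, the block-mate's sequence for both periods is known with probability 1.00, against 0.67 in blocks of 4 and 0.60 in blocks of 6. Half of the allocations (60 of 120) are complements of the one before on the list, against 33% and 25% determined by earlier block members in the larger blocks.

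This assumes that an allocation leaks, that the person who learns it knows the block size, and that envelope numbers can be matched to list positions. The article gives no frequency for code breaks or correct guesses, so the expected number of subjects affected cannot be stated. The harm is limited to treatment order and to unblinding of the paired subject. It does not invalidate the trial, but it is an avoidable weakness that should be corrected because doing so is cheap.

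**What to change.** - Generate the list with randomly varying larger blocks, for example 4 and 6.
- Keep the block sizes out of any document available to site staff.
- State that numbered envelopes are issued strictly in list order.

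The cost is a new list and one or two sentences of text. The only statistical price is a between-group difference of at most 3 subjects (half a block of 6) if recruitment ends mid-block, against at most 1 now.

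If randomisation has already begun, apply the new scheme to the remaining subjects and report the earlier use of blocks of 2 as a limitation.

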### Intervention

Subjects will be assigned CKJ or placebo group for 12 weeks. CKJ treatment group will be received 35 g CKJ (equivalent to 70 g of fresh CKJ) per day and they should consume a pack of the CKJ with three times a day after meals. The selection of the doses investigated in this study was based upon efficacy and safety data obtained from a previous human study [19]. Chungkookjang is provided by Sunchang Research Center for Fermentation Microbes (Sunchang, Republic of Korea), freeze-dried using a freeze-dryer, and then made into pills (Imshil Herbal Medicine Co., Imshil, Republic of Korea). Placebos were made with the same taste, appearance, and energy content but without the principal ingredient that was present in the CKJ. CKJ/placebo pills were provided to subjects every 6 weeks.

### Outcome measures

#### Primary outcome measurement

The primary outcome is the anthropometric parameter (weight, body mass index, body fat mass, percentage body fat, lean body mass, waist circumference, hip circumference, and waist to hip ratio).

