### Statistical analysis and sample size

#### Baseline data and outcomes data

Statistical analysis will be performed using SAS version 9.3 for Windows (SAS Institute, Cary, NC, USA). Data will be presented as mean values and standard deviation (SD). The Chi-square test will be performed to determine differences at baseline in frequencies of categorized variables between the groups. A linear mixed-effects model will be applied to repeated-measures data for each continuous outcome variable. Fixed effects will be included treatment group, treatment visit, and interaction between treatment group and visit. When the analysis of variance indicated significant differences among groups, post hoc test (Turkey’s test) will be used to separate the differences between groups before and after the 12-week intervention period. A value of p < 0.05 will be considered statistically significant.

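### The outcome section makes eight anthropometric measures primary, the sample-size section makes percentage body fat alone primary, and the two must be reconciled

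*Protocol article*

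**What the plan says.** Three parts of the Protocol article bear on what is primary.

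- **Primary objective:** "To evaluate the efficacy of the CKJ on anthropometric parameter in overweight/obese subjects after 12 weeks of consumption". No single measure is named.
- **The outcome section, on what is primary:** "The primary outcome is the anthropometric parameter (weight, body mass index, body fat mass, percentage body fat, lean body mass". Three girth measures (waist, hip and their ratio) complete the list, which makes eight variables.
- **Sample size:** the "primary outcome measure will be the percentage body fat", and "1.1% is assumed a clinically relevant difference between the two groups", with an SD of 2.78%, alpha 5% and power 80%, giving 50 subjects in each group and 120 enrolled.

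The analysis is set out under Baseline data and outcomes data: "A linear mixed-effects model will be applied to repeated-measures data for each continuous outcome variable", and "A value of p < 0.05 will be considered statistically significant". The only multiple-comparison device mentioned is a "post hoc test (Turkey’s test) will be used to separate the differences between groups before and after the 12-week intervention period". It compares groups and time points within one outcome. It does not act across outcomes.

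**The concern.** A trial has to say in advance which result makes it positive, and here two sections give different answers. Suppose percentage body fat shows no difference but waist circumference reaches p < 0.05. Under the outcome section, a significant primary outcome could be reported. Under the sample-size section, the primary outcome has failed. Nothing in the article says which section prevails.

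Two properties depend on the answer. One is the type I error of the primary conclusion, which is 5% for one named measure and higher if any of eight will do. The other is power: the 80% was worked out for percentage body fat and says nothing about the other seven measures. If the choice is left until the data are unblinded, it cannot be told apart from selection on the results.

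**Working it through.** **1. What the stated sample size covers.** Inputs from the Sample size section: difference 1.1, SD 2.78, alpha 5% (taken as two-sided, since the article does not say), power 80%. Reading 2.78 as a within-subject SD in a two-period crossover, the number per sequence is

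n = [SD × (z₀.₉₇₅ + z₀.₈₀) / difference]² = [2.78 × (1.960 + 0.842) / 1.1]² ≈ 50.1.

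This agrees with the stated 50 per group. It uses one endpoint and the full 5%, so the power statement belongs to percentage body fat only. The reading of the SD is an assumption, and the point made here does not depend on it.

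**2. Error rate if percentage body fat is the sole primary.** One test at 0.05 gives 5%.

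**3. Error rate if all eight are primary and any one suffices.** The article states no success rule for the eight, so this is conditional.

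- *Ceiling.* With eight independent tests, 1 − 0.95⁸ = 1 − 0.663 = 0.337. For jointly normal two-sided tests, correlation can only lower this (Šidák inequality).
- *Equal correlation.* Simulation of 400,000 sets of eight equally correlated two-sided z-tests; the correlations are assumed, as the article gives none:

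| Common correlation | Chance of at least one p < 0.05 |
|---|---|
| 0.3 | 30.0% |
| 0.5 | 25.0% |
| 0.7 | 19.0% |
| 0.8 | 15.8% |
| 0.9 | 11.9% |

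- *Actual structure.* Equal correlation does not describe these variables. In an adult of fixed height BMI carries the same information as weight. Weight is essentially fat mass plus lean mass. Percentage body fat is fat mass over weight. Waist-to-hip ratio is the quotient of two other listed measures. So the eight come from about four measured quantities. Simulating no effect with these links kept, and with changes in weight and each girth correlated 0.3 to 0.7 under several assumed fat and lean SDs, gives about 19–22%. Letting the assumed correlations run from 0 to 0.8 in a paired crossover analysis of 100 subjects gave 22–23%.

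**4. Comparison.** 20% against 5% is about four times the nominal level.

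**5. Alternative of keeping all eight.** Bonferroni would test each at 0.05 / 8 = 0.00625, and the family-wise error would be at most 5% (1 − 0.99375⁸ = 4.9% if independent). The 80% power, computed at 0.05, would then have to be restated.

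**The case against.** The strongest case on the other side has four parts.

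*The article already answers the question.* The sample-size section names one primary measure and gives its difference, SD, alpha and power. That shows what the designers probably meant, and it is why the fix follows that section. It does not settle the matter, because the section devoted to the primary outcome says otherwise and the primary objective agrees with it.

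*Adjustment across outcomes is normally left to the SAP.* This stands. The absence of a hierarchy or multiplicity rule from a condensed article is not a finding on its own. What an unseen SAP cannot do is agree with both definitions of the primary outcome.

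*The inflation is conditional and easily overstated.* A reader might infer that the trial, as written, carries a one-in-three risk of a false-positive primary result. The article does not support that. The 34% needs eight independent tests, and the list itself rules out independence. Even the figure of roughly one in five presupposes that any one significant measure counts as success, a rule the article neither states nor excludes.

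*The trial is preliminary.* The Discussion calls the study groundwork for a larger trial and leaves a confirmative conclusion to that trial. This lowers the harm of a false positive. But the trial still claims 80% power for a named primary measure, and a selected result would mislead the planning of its successor.

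**Conclusion.** The contradiction is in the text and has to be resolved: eight primary measures in the objective and outcome sections, one in the sample-size section. The type I error of the primary conclusion is 5% if the sample-size section governs. It is roughly one in five (about 19–22%) if the outcome section governs and any one significant measure counts as success. The latter range rests on assumed SDs and correlations, two-sided tests, and the arithmetic links among the measures; 34% is only the upper bound under independence. On either reading, the stated 80% power applies to percentage body fat and to none of the other seven.

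The case for requiring the change rests on the conflict between the definitions, not on the exact error rate. This point does not claim that the sample size is wrong.

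**What to change.** Amend the primary objective and the primary outcome section to agree with the sample-size section. Percentage body fat, CKJ versus placebo at Week 12, becomes the single primary outcome, tested at two-sided 5%. The other seven anthropometric measures move to the secondary outcomes, reported with confidence intervals and without a confirmatory claim. The sponsor should confirm this choice and record it before unblinding.

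Keeping all eight as primary with an adjusted alpha would also remove the conflict, but the power would have to be restated. The single measure is preferable because it is the only one for which the trial was sized.

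The cost is wording in two sections and, for the sponsor, giving up seven extra chances at a primary success. Sample size, visits and measurements stay as they are.
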